### Statistical Analyses

Baseline data collected from all participants will be summarized by treatment group, overall, and by ethnic-specific clusters (Māori and Pasifika). Information collected at the cluster level will also be reported. Continuous variables will be presented as numbers observed, means, and SDs. Categorical variables will be presented as frequencies and percentages. Since any differences between randomized groups at baseline could only have occurred by chance, no formal significance testing of baseline differences will be conducted.

The effect of the intervention will be evaluated using an intention-to-treat analysis including all clusters and participants in the group they are randomized to, regardless of whether they receive or complete that treatment. The proportion of participants who are adherent to lifestyle change (≥3 of 4 behaviors) at the end of the 12-week intervention period will be compared between the two treatment groups using generalized linear mixed models with a random cluster effect and adjusting for important baseline confounders. Missing participant data will be taken into account in the mixed model estimates by maximum likelihood, assuming they are missing at random. Similar regression analyses will be conducted on secondary outcomes using the link function appropriate to a continuous or categorical variable. Intracluster correlation coefficients will be estimated. Subgroup analysis will be conducted for Māori and Pasifika clusters separately. Statistical analysis will be performed using SAS 9.4 (SAS Institute Inc, Cary, NC, USA). All statistical tests will be two-sided at a 5% significance level.

**Table 1 table1:** Schedule of enrollment, interventions, and assessments.

Time point		Enrollment (Week 0)		Allocation (Week 0)	Postrandomization (Week 4)	Close-out (Week 12)
**Enrollment**						
	Eligibility screen	X^a^				
	Informed e-consent^b^	X				
	Contact details	X				
**Interventions^c^**						
	OL@-OR@ mHealth tool		X		X	X
	Wait-list control		X		X	X
**Assessments**						
	Age, sex, ethnicity		X		X	X
	Socioeconomic details		X		X	X
	Contact details		X		X	X
	Smoking behavior		X		X	X
	Physical activity		X		X	X
	Alcohol intake		X		X	X
	Fruit and vegetable intake		X		X	X
	Anthropometry (self-reported weight, height)		X			X
	Health status		X			X
	Medication use		X			X
	Kava consumption		X			X
	Holistic wellbeing		X			X
	Pacific and New Zealand heritage and lifestyle^d^		X			X
	Click depth index					X
	Loyalty index					X
	Interaction index					X
	Recency index					X
	Feedback index					X

^a^X indicates the presence of assessments required at particular time periods during the trial.

^b^Consent using a computer-based consent form.

^c^Intervetion was continuous from week 0 to week 12.

^d^Pasifika participants only.

### Engagement Index

Basic descriptive data analysis will be performed on the metrics and components of the engagement index as well as the final index score [44]. To analyze the index score, cutoff points will be developed based on the distribution of the index scores of the total sample using tertiles. Participants will be categorized as either poorly, moderately, or highly engaged. Group comparisons between poorly, moderately, or highly engaged participants will be conducted using generalized linear mixed models. Additional analyses will be performed to determine the association between the index and sociodemographic characteristics of the participants including their education level, ethnicity, age, annual household income, device type (Android or iOS), and system type (app only, Web only, or app and Web).

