### Secondary Outcome Measures

Secondary outcome measures will be collected at 4- and 12-week follow-up assessments via a Web-based questionnaire and include the same health behavior outcomes as those assessed at baseline (physical activity, smoking, alcohol intake, and fruit and vegetable consumption) and holistic wellbeing. At 12-week follow-up, user engagement and interaction with the mobile phone app will be quantified using an engagement index [44]. The index is an adapted version of the Web Analytics Demystified Visitor Engagement Index [45]. The original index comprised 7 subindices (click depth, loyalty, recency, interaction, feedback, brand, and duration indices). Although measuring all indices is ideal, the Web Analytics Demystified Visitor Engagement Index protocol emphasizes that the calculation can be adapted to suit the project [45]. Therefore, in line with a previous study assessing user engagement of an mHealth intervention [44], we will select relevant Web metrics to develop a composite engagement index for users of the OL@-OR@ tool. These metrics will include session duration, page views per session, and the number of push notifications. They will be used to calculate the following subindices: (1) click depth index: the number of pages participants view per session in the app, (2) loyalty index: the frequency of participants accessing the app after they commence the intervention, (3) interaction index: the number of push notifications sent through the app that are opened, (4) recency index: time lag between each session when the participant accessed the app, and (5) feedback index: self-reported 20-item measure of participant satisfaction with the app (questions relate to ease of navigation, usefulness of information, helpfulness of notifications, and satisfaction with the look of the app) [44].

The overall engagement index summarizes the subindices from date of registration to 12-week follow-up. The overall index will provide a score for each participant that measures overall engagement with the app during this period. Cutoff points will be developed based on the distribution of the total sample’s index scores using tertiles. Participants will then be categorized as either poorly, moderately, or highly engaged. A summary of all assessments and the stage at which each will be measured is outlined in Table 1.

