### Sample Size

Recruiting 640 participants (16 clusters per arm, 32 clusters in total) will provide 80% power at a 5% level of significance (two-sided) to detect a between-group difference of 15% in the primary outcome at 12 weeks postrandomization, assuming the proportion of participants adherent to healthy lifestyle behaviors in the control group is 30% [43] and an intracluster correlation coefficient of 0.05 [46]. The inflation factor is approximately 3, that is, (1+40−1×0.05), which inflates n=160 per arm in a standard randomized controlled trial to n=480 per arm in a cluster-randomized trial under the same assumption. However, we aim to recruit 1280 participants in total from 64 clusters (32 Māori clusters and 32 Pasifika clusters). This sample size will provide 80% power for the analysis of Māori and Pasifika participants separately if our recruitment target is met.

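### The stated engagement group comparisons use sample tertiles of a per-participant index score, which generally discards information that a continuous term would keep

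*Protocol article*

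**What the plan says.** Under Secondary Outcome Measures, the protocol article builds an engagement index from five subindices (click depth, loyalty, interaction, recency and feedback) and states: "The overall index will provide a score for each participant that measures overall engagement with the app during this period". The same section then cuts the score at sample tertiles: "Participants will then be categorized as either poorly, moderately, or highly engaged".

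The Engagement Index section makes the cut part of the analysis: "To analyze the index score, cutoff points will be developed based on the distribution of the index scores of the total sample using tertiles". The inferential step follows: "Group comparisons between poorly, moderately, or highly engaged participants will be conducted using generalized linear mixed models".

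Two other sentences in that section concern the index without saying that it is cut. One is descriptive: "Basic descriptive data analysis will be performed on the metrics and components of the engagement index as well as the final index score". The other reads "Additional analyses will be performed to determine the association between the index and sociodemographic characteristics of the participants", and goes on to list education, ethnicity, age, income, device type and system type.

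The article gives no distribution, range, effect size or power for any engagement analysis. It does not name the variable on which the three groups will be compared, or say whether the contrast is a trend or an overall three-group test.

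**The concern.** The score is in hand for every participant before it is cut. After the cut, two people just either side of a tertile count as different, and all those within a third count as the same. The cut points come from this sample's own distribution, and the article gives no external or validated threshold for them.

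The only analysis explicitly assigned to the uncut final score is descriptive, while the stated group inference rests on the thirds. For efficiency one would normally do the reverse. At stake is the precision of the group comparisons for a named secondary outcome. The tertiles are a stated method rather than a detail left open, so they can be assessed from the article alone.

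**Working it through.** **The plan's own figure.** There is none to reproduce. The article's only power statement, "to detect a between-group difference of 15% in the primary outcome at 12 weeks postrandomization", concerns another endpoint. What follows is therefore a relative comparison, anchored by assumption at 80% power for the continuous index.

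**Inputs.**
- From the article: three groups cut at sample tertiles, so about one third each; "All statistical tests will be two-sided at a 5% significance level".
- Assumed: the shape of the index; an association linear in the score; 80% power for the continuous linear test. Clustering is ignored, so the results show relative efficiency and not the power of this trial.

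**Step 1: information kept, normal index.** For a standard normal variable the tertiles lie at ±0.4307. The mean of an outer third is ±3φ(0.4307) = ±1.09, and the middle third has mean 0. The share of variance kept by the group means is (2/3) × 1.09² ≈ 0.793, so about 20.7% is lost.

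**Step 2: power.** The non-centrality for 80% power at two-sided 5% on 1 df is (1.960 + 0.842)² ≈ 7.85. After the cut it is 7.85 × 0.793 ≈ 6.22. The non-central chi-square distribution then gives:
- trend across tertiles, 1 df: power 0.704;
- three-group comparison, 2 df: power 0.601. Part of this fall comes from the extra degree of freedom.

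**Step 3: other assumed shapes**, each with an association linear in the raw score. The first column uses the group means and feeds the 2-df power; the second uses scores 1, 2, 3 and feeds the trend power.

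| Assumed index | Kept, group means | Kept, scores 1-2-3 | Power, trend | Power, 2 df |
|---|---|---|---|---|
| U-shaped beta (0.5, 0.5) | 0.912 | 0.912 | 0.763 | 0.666 |
| Uniform | 0.889 | 0.889 | 0.752 | 0.654 |
| Normal | 0.793 | 0.793 | 0.704 | 0.601 |
| Gamma, shape 2 | 0.716 | 0.693 | 0.645 | 0.555 |
| Exponential | 0.649 | 0.608 | 0.589 | 0.512 |
| Lognormal, sigma 1 | 0.398 | 0.357 | 0.387 | 0.333 |

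By group means the loss runs from 1 − 0.912 = 0.088 to 1 − 0.398 = 0.602, that is, about 9% to 60%. The large losses need an association that is linear in a skewed raw score. Tertile membership does not change under a monotone transformation, so if the association with a lognormal index is linear in its logarithm, the normal row applies.

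**Step 4: non-linear associations, normal index.**
- *Step at the upper tertile.* A linear term captures 0.594 of the effect variance and the tertiles 1.000. With the linear term at 80% power, the non-centrality for the tertiles is 7.85 / 0.594 ≈ 13.2, and the 2-df power is 0.913. Here the tertiles do better.
- *Step at the median.* The shares are 0.636 and 0.667; with the linear term at 80%, the 2-df tertile test has 0.730.
- *Symmetric U-shape.* A linear term captures essentially nothing and the tertiles 0.220. A purely linear term would fail here, so a check of linearity has to come with the continuous term.

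**The case against.** The strongest case on the other side is that this is an efficiency preference on a low-stakes analysis. The article says its index follows a previous mHealth engagement study. Engagement is a secondary measure with no stated power. No statement in the article is false because of the tertiles, and an analysis plan that is not shown may add continuous modelling. Most of this is fair, and it sets the weight of the point. It does not remove the point, because the article itself fixes tertile groups as the basis of the group comparisons.

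Several stronger readings are tempting, and the documents do not support them:

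- *Every engagement comparison loses power.* The sociodemographic analyses refer to the index and are not said to use the thirds, and the final score is itself summarised.
- *The loss is a fixed fifth.* That needs a normal index and a linear association, and the article gives neither. Metrics such as page views, session frequency and time lags may be skewed. If the total sample includes control participants, who have only the data-collection version, the scores may be a mixture of two distributions.
- *Power must fall.* With a step at a tertile it can rise.
- *The comparisons are how the trial would relate use of the tool to its outcomes.* The Engagement Index section names no outcome for them.
- *A continuous score would make results comparable across studies.* The index is adapted to this project, and a score standardised within this sample is just as specific to it.

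**Conclusion.** The point holds as a narrow, optional efficiency improvement. The stated group comparisons replace a per-participant score by sample thirds, which generally costs information. With a roughly normal index and a linear association the cost is about a fifth, and 80% power becomes about 70% (trend) or 60% (2 df). Across the other shapes examined, still with a linear association, the loss is about 9% to 60%. These figures are relative illustrations: the article supplies no distribution, effect size or power for engagement, and a threshold at a tertile would reverse the direction. The primary outcome, its analysis and the sample size do not depend on this choice.

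**What to change.** In the Engagement Index section, state that inference for the engagement comparisons rests on the index as a continuous term in the same mixed models, with linearity checked and a spline or transformation used if the association is not linear. Keep the tertile groups for descriptive tables or as a supporting display. The same sentence can say whether the sociodemographic analyses use the score or the thirds.

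The cost is about one sentence, with the same data and models. The downsides are small: a linearity check, a less simple presentation than three labelled groups, and possibly less power than tertiles if the true relation is a step at a tertile.

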### Data Management

Data from the trial will be entered into the Drupal database at the study center (National Institute for Health Innovation, University of Auckland, New Zealand). Information about study subjects will remain confidential in keeping with the obligations set out in the Privacy Act 1993, the Health Information Privacy Code 1994 and Section 22B-221 of the Health Act 1956. Access to all study data will be restricted to research staff directly involved in conducting or monitoring the study. Confidentiality will be protected using study registration numbers, and only aggregated and deidentified data will be reported. Computerized information will be password protected, and hard copy information (such as cluster agreements) will be kept in a locked filing cabinet under the responsibility of community coordinators. All reports from the study will be written such that no individuals can be identified. Paper records, electronic files, and source documents will be retained for 6 years from the termination date of the study, in accordance with the requirements of the Privacy Legislation and the Health (Retention of Health Information) Regulations 1996.

### Ownership of Data

Individual study data will remain the property of individual study participants. The study center will have the responsibility for storage, protection, and retrieval of the study data. The University team will have the responsibility for the safe guardianship and use of the data in consultation with the wider project team. The Māori community partners will have guardianship over the data for Māori participants. Access to the data, all analyses, and dissemination of the data will be the joint responsibility of the University team and the Māori Community partners. Māori community partners will review and interpret all analyses involving Māori data and agree on key findings before dissemination.. The same principles apply to data for Pacific participants where Pacific community partners will have guardianship.

### Ethical Approval and Informed Consent

Ethics approval for the trial was obtained from the Northern B Health and Disability Ethics Committee of New Zealand (17/NTB/152/AM01, approved on November 17, 2017). Ethics approval for any amendments to the study protocol will be sought prior to the implementation of the changes (information on the trial registry will be updated accordingly). Maintenance of confidentiality and compliance with the Privacy Act will be emphasized to all study participants. Study participation will be entirely voluntary, and participants may withdraw from the study at any time, without having to provide a reason, by contacting the research team. A participant information sheet and consent form will be given to participants who are identified as being part of a cluster by the local community coordinator during an information meeting. E-consent will be obtained at the time of registration once participants have had the opportunity to read the participant information sheet and ask any questions to their local community coordinator or other members of the study team. If any participants suffer harm from trial participation (which is unlikely), they should be eligible for compensation via their private health or life insurance or via New Zealand’s Accident Compensation Corporation scheme.

### Trial Governance

Trial governance includes a steering committee (on which all authors sit) and a trial management team who will manage the day-to-day processes of the trial, including data management. This trial does not meet two or more of the criteria required for the establishment of a Data Safety and Monitoring Committee [47].

### Dissemination Policy

Results will be disseminated regardless of the magnitude or direction of treatment effect. Dissemination will include adding trial results to trial registration within 1 year of trial completion, feedback to trial participants, publication in an international journal and national and international media releases (including Māori, Pacific, and mainstream media channels) at the time of journal publication, and presentations to participating communities and relevant local, national, and international audiences (including health service funders and providers). In New Zealand, this will include but will not be limited to the Ministry of Health, District Health Boards, Māori and Pacific health provider organizations, general primary health organizations, nongovernment organizations, and health professionals. Criteria for authorship of any papers arising from the trial will be taken from the International Committee of Medical Journal Editors [48].

### Extended Follow-Up of Study Participants

Longer-term follow-up (beyond the 12-week follow-up period of the trial) will be via the New Zealand Integrated Data Infrastructure (IDI) [49]. Participants will be asked if they consent to data gathered in this trial being linked to IDI using their unique national identifier to facilitate longer-term follow-up and assessment of health information that may be influenced by this study, for example, blood tests (blood glucose and cholesterol), visits to health professionals, and diabetes and heart disease medication use. IDI is a large national database containing microdata about people and households in New Zealand. Data is derived from a range of government agencies, Statistics New Zealand surveys, and nongovernment organizations. We have ethics approval to examine such data once a year for a maximum of 5 years after the study ends. All information will be anonymized and will not be linked to information that could identify participants. Written consent will be sought from study participants.

## Results

Trial recruitment opened in January 2018 and will close in July 2018. Trial findings are expected to be available early in 2019.

## Discussion

Most mHealth interventions are designed with minimal input from end-users and lack tailoring to specific (cultural) needs [50]. A culturally-tailored mHealth tool (mobile phone app plus website) aimed at supporting healthier lifestyles among Māori and Pasifika communities in New Zealand was co-designed by an academic and community partnership team [24]. This ground-up work informed a theory-driven approach to content development, including identification of key themes and content domains, selection of behavioral determinants and change techniques, and development of features and functionalities of the mHealth tool.

Comparable user-centered principles were applied to co-designing a community-led, cluster-randomized, wait-list controlled trial to evaluate the impact of the mHealth tool on health behavior change. As such, this project is engaging with communities in a meaningful way throughout the research process, from development to evaluation of the mHealth intervention. This approach has not only resulted in an mHealth tool that aligns with the needs, wants, and lived (cultural) contexts of Māori and Pasifika communities but also anticipated increased engagement and empower communities to make positive lifestyle changes.

## Appendix

Multimedia Appendix 1 SPIRIT checklist.

Multimedia Appendix 2 Trial cluster locations in New Zealand.

Multimedia Appendix 3 Screenshots of OL@-OR@ app.

Multimedia Appendix 4 Motivational Messages.

Multimedia Appendix 5 Control App.

Multimedia Appendix 6 Peer-review report from the funding agency.

## Abbreviations

IDI: Integrated Data Infrastructure
